## 4. Objectives

### 4.1 General Objective:

To evaluate the feasibility and acceptability of bubble CPAP in treating childhood severe pneumonia initially in two tertiary followed by two district hospitals (stages I and II) and finally to assess the effectiveness of bubble CPAP in reducing treatment failure in children with severe pneumonia in stage III compared with the WHO standard low-flow oxygen therapy among children hospitalized with severe pneumonia and hypoxemia in Ethiopia.

### 4.2 Specific Objectives

#### Primary Objectives

- To determine the effectiveness of bubble CPAP in reducing treatment failure in children admitted to hospital with severe pneumonia and hypoxemia compared to using WHO standard flow oxygen therapy up to the maximum flow that can run through nasal oxygen cannula in frontline district hospitals.
- To determine therapeutic effectiveness of bubble CPAP compared to WHO standard low flow oxygen in reducing treatment failure and mortality in children aged 1-12 months admitted to hospitals with severe pneumonia and hypoxemia

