#### Secondary Objectives

- To assess the feasibility, acceptability, and safety of bubble CPAP in treating childhood severe pneumonia in two tertiary hospitals in Stage I, in two district hospitals in Stage II

- To examine the programmatic and behavioral acceptability of bubble CPAP at various health care levels (primary to tertiary) in Ethiopia in first two stages
- To identify and predict implementation level challenges and bottle necks of scaling up bubble CPAP to district level facilities
- To determine the effectiveness of bubble CPAP in reducing deaths in children admitted to frontline district hospitals with severe pneumonia and hypoxaemia compared to WHO standard flow oxygen therapy up to the maximum flow that can run through nasal oxygen cannula.

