## Primary outcome

The primary outcome of the study is treatment failure. According to this protocol treatment failure will be declared if any of the following criteria is met:

- B. Presence of severe hypoxemia ( $\text{SpO}_2 < 85\%$ ) at any time after at least one hour of intervention plus respiratory distress when the child is receiving BCPAP/LF  
OR,
- C. If the patient developed the indication of mechanical ventilation when the child is receiving BCPAP/LF  
OR,
- D. If the patient died during hospitalization or within 72 hours of left against medical advice (LAMA)  
OR,
- E. If the patient left against medical advice (LAMA) when the patient is still on study intervention

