## Sample and sampling procedure:

In this trial, our recruitment goals are approximately a total of 1240 children (620 children each for LF oxygen and bubble CPAP therapy) for a power of 80% and effect size of 50% (reduction of treatment failure, primary outcome of the study, from chart analysis 10% treatment failure in 2019 in comparison facilities) for 12 clusters (103-104 patients in each cluster), adjusted for a intra-cluster correlation coefficient (ICC) level of 0.003 required for cluster randomization. For the calculation of sample size we have used following formula:

Where,  $DF$ , Design effect =  $1 + \delta(m-1)$  [here  $DF=1.52$ ],

$n_1$  = Required minimum sample size per arm,  $\delta$  = the inter cluster correlation,  $m$  = the number of patients in each cluster [103.3 in this study],

$P_1$  = the percentage of treatment failure of children with pneumonia receiving standard treatment (low flow) = 10%,

$P_2$  = the expected percentage of treatment failure of children with pneumonia who will receive intervention (bubble CPAP) = 5% [we have observed 5% treatment failure in two district hospitals during the stage II of our study which correspond 50% effect size],  $Z_\alpha$  = the z-score value [here,  $Z_\alpha = 1.96$  at 5% level of significance],  $Z_\beta$  = the z-score value [here,  $Z_\beta = 0.84$  at 80% power]. We are intending to enroll same number of children (103-104) having our eligibility criteria from each hospital (cluster) irrespective of receiving intervention (bubble CPAP) or standard treatment (low flow).

As a run-in period we will enroll 2 participants in each hospital which will be excluded from final analysis.

**Data collection:** Data will be collected by individual patient assessment through systematic observations using a structured questionnaire. Socio-demographic and different clinical data will be collected. The questionnaire will include the baseline characteristics, intervention and outcome data. All study data will be collected by dedicated study personal at sites.

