## Study setting

The study will be done in the 12 district hospitals (6 in each arm) which are part of the effectiveness study.

**Data analysis:** Quantitative data will be analyzed using STATA -14 following the principle of intention to treat. Treatment failure and/or death will be analyzed using  $\chi^2$  or Fisher's exact tests. Primary and secondary outcomes will be compared by calculating relative risks (RRs) at 95% confidence interval. Log-linear binomial regression will be applied to identify the predictors of primary and secondary outcomes after adjusting for potential confounders. Continuous variables will be analyzed using the Mann-Whitney test.

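### Section 4.2 ranks treatment failure and mortality at 1-12 months as a primary objective, although the protocol defines and sizes a single primary outcome, treatment failure in all children

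*Protocol*

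**What the plan says.** Section 4.2 of the protocol has two bullets under Primary Objectives. The first is "To determine the effectiveness of bubble CPAP in reducing treatment failure in children admitted to hospital with severe pneumonia and hypoxemia". The second is an effect "in reducing treatment failure and mortality in children aged 1-12 months admitted to hospitals with severe pneumonia and hypoxemia". The Summary repeats the second bullet among its Stage III objectives, without a primary or secondary label.

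Elsewhere the protocol names one primary outcome:

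- Stage III, Primary outcome: "The primary outcome of the study is treatment failure", with no age restriction. The Methodology and Statistical Analysis rows of the Summary agree, and the general objective (4.1) also speaks only of treatment failure.
- Stage III, Sample and sampling procedure: 620 children per arm "for a power of 80% and effect size of 50" percent in treatment failure, 10% v 5% in all children, "at 5% level of significance".
- Section 4.2, Secondary Objectives: "To determine the effectiveness of bubble CPAP in reducing deaths in children admitted to frontline district hospitals with severe pneumonia and hypoxaemia". The Stage III list of secondary outcomes also contains death.
- Section 2 (last paragraph) and section 3 (question 2) say the reverse: death is primary and treatment failure secondary.
- Stage III, Data analysis: "Primary and secondary outcomes will be compared by calculating relative risks (RRs) at 95% confidence interval".

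The protocol gives no infant share of enrolment, no infant failure rate and no mortality rate for the Stage III comparison.

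**The concern.** As section 4.2 stands, mortality in a subgroup ranks above mortality in the whole trial population, and a subgroup result for treatment failure ranks level with the result the trial was sized for. The sections on the primary outcome and sample size contradict that ranking, and sections 2 and 3 contradict both.

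What is at stake is the main claim. Someone reading section 4.2 could report a significant result in children aged 1-12 months as success on a primary objective when overall treatment failure is not significant. That raises the chance of a false primary claim. In the other direction, a non-significant infant result could be read as failure on a primary objective that the trial was never sized to answer.

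**Working it through.** **1. The plan's own figure rests on one hypothesis.** Inputs from Sample and sampling procedure: 10% v 5%, z = 1.96 and 0.84, ICC 0.003, 103.3 children per cluster. The formula is not legible in the text at hand, so variants were tried.

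- Pooled-variance formula per arm: [1.96·√(2·0.075·0.925) + 0.84·√(0.09 + 0.0475)]² / 0.05² = 434.4, so 435.
- With continuity correction: (n/4)·[1 + √(1 + 4/(0.05n))]² = 473.6, so 474.
- Design effect: 1 + 0.003 × 102.3 = 1.3069.
- 474 × 1.3069 = 619.5, so **620**, as stated. Without the correction the result is 435 × 1.3069 = 569.

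The whole sample is used up by overall treatment failure. Its power at 620 per arm is 80% with the correction and 83% without.

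The protocol also prints a design effect of 1.52. That corresponds to an ICC of 0.52/102.3 = 0.0051, so the range 0.003-0.0051 is used below.

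**2. Error rate if the infant objective were tested as primary at an unadjusted 5%.** Assumptions, none of them in the protocol: infants are a fraction f = 0.5-0.7 of enrolment, and the infant failure and infant death statistics correlate at r = 0.5-0.7. The overall and infant failure statistics correlate at √f, and overall failure and infant death at r·√f. Family-wise error is 1 − P(all |Z| < 1.96), integrated over the infant failure statistic.

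| f | two failure tests | three tests, r = 0.5 | three tests, r = 0.7 |
|---|---|---|---|
| 0.5 | 8.3% | 12.2% | 11.4% |
| 0.6 | 8.0% | 11.8% | 11.0% |
| 0.7 | 7.6% | 11.4% | 10.6% |

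**3. Power for infant treatment failure.** The 10% v 5% rates are assumed to hold in infants. Infants per arm = 620f, over six hospitals. Design effect = 1 + ICC·(620f/6 − 1). Effective n = 620f / design effect. Power = Φ{[√n·0.05 − 1.96·√0.13875] / √0.1375}. For the continuity-corrected version, n is replaced by (n − 20)²/n, where 20 = 1/0.05.

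| f | ICC | infants per arm | design effect | effective n | z | corrected |
|---|---|---|---|---|---|---|
| 0.5 | 0.0051 | 310 | 1.258 | 246.3 | 56% | 49% |
| 0.5 | 0.003 | 310 | 1.152 | 269.1 | 60% | 53% |
| 0.7 | 0.0051 | 434 | 1.364 | 318.2 | 67% | 61% |
| 0.7 | 0.003 | 434 | 1.214 | 357.5 | 72% | 67% |

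**4. Power for infant mortality.** Rates of 5% v 2.5% are assumed, since the protocol gives none. With the same effective n, power = Φ{[√n·0.025 − 1.96·√0.0721875] / √0.071875}: 31% at the lowest effective n (246.3) and 42% at the highest (357.5).

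**5. What 80% power in infants would need.** At ICC 0.003 and 10% v 5%, about 620 infants per arm. If infants were 60% of enrolment, that is 620/0.6, or about 1,033 children per arm.

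**The case against.** The best defence is that the operative sections are clear. The Primary outcome section, the Summary, the general objective and the sample size all name treatment failure in all children, and the 5% level appears once, for that outcome. No passage says that the trial succeeds on the infant objective. This stands.

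A reader might infer that the protocol prescribes three primary tests at 5% each, with the error rate about doubled. The documents do not support that as fact:

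- Treatment failure and mortality are joined in one bullet and can be read as one question, which leaves two tests.
- Had all objectives to succeed, the error would not inflate at all, although power would be lower still.
- A split or an order of testing may stand in a statistical analysis plan that is not shown, so its absence here is no fault.

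The error rates above are therefore conditional. The power figures are conditional too: infants may have higher or lower failure rates than the 10% given for all children. It is also fair that the 80% is tied expressly to the primary outcome of the study, so the protocol does not claim it for infants.

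What the defence does not remove is the ranking itself. The order of objectives and the basis of the sample size are fixed in this protocol. An analysis plan could control the error rate, for instance by testing infants only after a significant overall result. It could not supply the missing power.

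**Conclusion.** The contradiction is real and lies in the protocol text: a primary objective in section 4.2 has no counterpart in the primary outcome or the sample size, and infant death outranks death in all children. Sections 2 and 3 add a third version, with death primary.

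The consequences depend on how the infant objective would be used. Tested as primary at an unadjusted 5%, it takes the family-wise error from 5% to about 7.6-8.3% with two tests, or about 10.6-12.2% with three. On the rates and shares assumed, power for infant failure is about 56-72% (z) or 49-67% (continuity-corrected), and for infant mortality about 31-42% (z). All are below the planned 80%. The contradiction rests on none of these assumptions; the percentages do. It should be corrected, but it does not touch the comparison of overall treatment failure itself.

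**What to change.** Four edits to the protocol text:

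1. In section 4.2, move the 1-12 month bullet from Primary to Secondary Objectives as a pre-specified subgroup, reported with cluster-adjusted confidence intervals. An arm-by-age interaction test is optional.
2. In the Summary, label the same Stage III objective as secondary. It carries no rank there now.
3. In the last paragraph of section 2, correct the sentence that makes death primary and treatment failure secondary.
4. In section 3, question 2, make the same correction.

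Moving the bullet alone is not enough, because sections 2 and 3 would still name death as primary. After all four edits, treatment failure in all children is the single primary outcome, tested at 5%, throughout.

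The cost is an amendment to the wording, with no new data and no change in sample size. The downside is that no confirmatory claim can be made for infants alone, for which the trial was not sized. Keeping the infant objective primary with a split level would cost more: at 620 per arm, with ICC 0.003 and the continuity correction, power for overall failure falls from 80% to about 71% at a level of 0.025 and about 66% at 0.0167.

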#### Secondary Objectives

- To assess the feasibility, acceptability, and safety of bubble CPAP in treating childhood severe pneumonia in two tertiary hospitals in Stage I, in two district hospitals in Stage II

- To examine the programmatic and behavioral acceptability of bubble CPAP at various health care levels (primary to tertiary) in Ethiopia in first two stages
- To identify and predict implementation level challenges and bottle necks of scaling up bubble CPAP to district level facilities
- To determine the effectiveness of bubble CPAP in reducing deaths in children admitted to frontline district hospitals with severe pneumonia and hypoxaemia compared to WHO standard flow oxygen therapy up to the maximum flow that can run through nasal oxygen cannula.

## 5. Methods

### 5.1 Study Stages:

Stage I. Testing feasibility, acceptability, and safety of locally constructed bubble CPAP in tertiary hospitals

Stage II. Investigation of feasibility, acceptability, and safety of bubble CPAP in frontline, district hospitals

Stage III. To evaluate the comparative therapeutic effectiveness of bubble CPAP compared to low flow oxygen in frontline, district hospitals

### 5.2 Detailed Description of Methods and Materials

**Stage I.** Testing feasibility, acceptability, and safety of locally constructed bubble CPAP in tertiary care hospitals

**Study Design:** During this Stage feasibility/demonstration stage will be done as a pilot in 3 hospitals where we will evaluate current treatment practice, facilities, and operational challenges for the introduction, clinical use and maintenance of bubble CPAP. Children with severe pneumonia and hypoxemia diagnosed by hospital physician will be enrolled consecutively and put on bubble CPAP. To have this enrolment among the eligible children, we will follow the WHO recommended “Management Algorithm of Children 1-59 months with Acute Respiratory Infections” (Annex 14)

**Study setting:** The study will be conducted at Tikur Anbessa, St. Paul's Millennium and Yekatit 12 Medical College hospitals. The hospitals are located in Addis Ababa, Ethiopia. All the hospitals are tertiary teaching hospitals. An average of 80-100 under five children with severe pneumonia are admitted to St. Paul's Millennium Medical College Hospital & Yekatit 12 hospital and 30-40 patients in Tikur Anbessa Specialized Hospital each month. The current practice of oxygen delivery methods in both hospitals is via low flow oxygen therapy and occasional use of locally constructed bubble CPAP for selected patients based on clinicians' decision. Children with severe pneumonia are also placed on IV antibiotics and other supportive care including maintenance fluid. Children will be placed on mechanical ventilators if they have any specific indication. The indications for mechanical ventilation are acute or chronic respiratory failure, which is defined as insufficient oxygenation, insufficient alveolar ventilation, or both. It can result from several conditions such as pneumonitis (infectious, aspiration), ARDS, cardiogenic pulmonary edema, upper airway obstruction (croup, laryngeal angioedema), lower airway obstruction (severe acute asthma), hypoventilation (drug overdose, Guillain Barre syndrome), severe sepsis and septic shock (25).

#### **Inclusion criteria**

- Age between 1 month and 59 months,
  - Meet WHO clinical criteria for severe pneumonia (these include a child with cough or difficulty in breathing and any of the danger signs below
  - Hypoxemia (oxygen saturation <90% or central cyanosis)
  - Grunting
  - inability to breastfeed or drink, lethargy or reduced level of consciousness, convulsions)
- Hypoxemia (oxygen saturation <90% in room air) is a must criteria
- Parent/guardian gives informed consent to participate in the study

#### **Exclusion criteria**

- Known congenital heart disease, asthma, or upper-airway obstruction
- Tracheostomy

- Pneumothorax
- Needs mechanical ventilation for any specific reason as decided by the clinician

### **Primary outcome**

The primary outcome of this Stage of the study is the feasibility and acceptability of using bubble CPAP both at the patient level and at the health professional level in tertiary care hospitals

### **Sample and sampling procedure**

This is a pre-implementation study aiming to test acceptability and feasibility of using bCPAP. So, we will use a convenient sampling technique. Thirty eligible children will be enrolled at this stage of the study from each site. All children who fulfill the inclusion criteria and whose parent/guardian give consent will be enrolled consecutively until the required sample size is reached.

**Stage II.** Testing feasibility, acceptability, and safety of locally constructed bubble CPAP in frontline, district hospitals

**Study Design:** During this stage children with severe pneumonia and hypoxemia will be enrolled consecutively and placed on bubble CPAP.

**Study setting:** This stage of the study will be done in two district hospitals to assess the applicability of bubble CPAP in less intensive facilities in the context of district level hospitals (where there is less manpower and equipment). The standard of care in these hospitals regarding oxygen delivery is low flow oxygen therapy.

**Inclusion & Exclusion criteria** are the same as Stage I.

### **Sample and sampling procedure**

This part of the study aims to collect data on operational challenges before the major implementation trial so a convenient sampling will be used. Twenty illegible children will be enrolled at this stage of the study at each site. All children who fulfill the inclusion criteria

and whose parent/guardian give consent will be enrolled consecutively until the required sample size is reached.

**Primary outcome** –The same as with Stage I.

**Qualitative methods for Stages I and II:**

### **Qualitative Assessment**

As part of a mixed-method approach, in Stage I a qualitative evaluation will be used alongside quantitative assessment to explore potential early operational challenges and opportunities for the introduction, clinical use and maintenance of bubble CPAP in order to rolling out and implementation of this innovative therapy in other public hospitals in Stage III after addressing all the challenges found in Stages I and II.

This qualitative assessment will be implemented through a participatory approach by actively engaging all stakeholders including consumers or beneficiaries, hospital health workers, clinicians, pediatricians, researchers and policy makers. The proposed participatory qualitative method will recognize that people within communities are best placed to identify the operational challenges and facilitators of BCPAP. The aim of this integrated approach is to provide the flexibility to fill in gaps in the available information, to provide different perspectives on complex, contextual, and multi-dimensional phenomena.

### **Qualitative data collection**

Data will be collected concurrently in different episodes of quantitative assessment in Stages I and II. We will conduct interviews with individuals (e.g., a combination of key informant interviews and in-depth interviews) and groups (e.g. focused group discussions). Moreover, observation technique may be considered if interviews do not provide sufficient insights. The rationale of conducting Key Informant Interviews, In-depth Interviews, Focus Group Discussion (FGD) and Observations are described below.

#### ***Key Informant Interview***

The rationale of choosing key informant interview for this study is to understand the health system issues related to the implementation of BCPAP in hospital settings, which will help to explore enabling policy environment in order to reach the project's goals. In addition, the key informant interview will help to recognize potential target population for in-depth interviews and FGDs, identify issues that may need further investigation, clarify survey findings, and generating study recommendations. The key informant will be selected from different level including hospital administrators, pediatricians and other policy level

stakeholders who will be knowledgeable about the particular issue related to study subject and influential in decision-making. In each Stage (I & II), 8-10 key informants will be interviewed; however, actual number will be determined based on data saturation and availability of informants.

### *In-depth Interview*

The in-depth interviews will be conducted with patients' caregivers (who will be responsible for caring of the child during hospitalization; sometimes also called patient's attendant), research staff and hospital staff (physicians, nurses - who will directly provide the treatment) to understand the operational challenges and opportunities from their real life experience of introduction of BCPAP treatment. Their perceptions, motivation and attitude are important as they will be closely involved in receiving and providing the treatment. This interview will also help to explore additional-specific issues that might be supplemented with new information and clarify complex survey results. Additionally, in-depth findings from this interview will be used to triangulate to strengthen the validity of other findings from other data collection techniques. In each Stage (I & II), 10-15 in-depth interview will be conducted and numbers of interviews will be distributed equally in each of the study sites, however, actual number will be determined based on data saturation against explored board themes.

### *Focus Group Discussion (FGD)*

The FGD will help to understand the willingness, affordability issues, and acceptance and to generate study recommendations for the introduction of BCPAP perfectly in the public health facilities. The FGD will be conducted with patient's guardians who play an important role in decision making related to treatment of the child and hospital staff. In each Stage (I & II), 8 FGDs will be conducted; however, actual number will be determined based on data saturation.

